### Eligibility Criteria

The eligibility criteria for women and midwives are presented in Textboxes 1 and 2. The medical note audit will include women who received directed pushing during the second stage of labor and met the same eligibility criteria as the women in the spontaneous pushing group.

Eligibility criteria for women.
**Inclusion**
**criteria**
Older than 18 years of ageGestation 37+ weeks at birthSingle, healthy fetus in cephalic presentationNo complications during labor
**Exclusion criteria**
Administered epidural analgesiaAny medical or obstetric complication affecting second-stage managementUnable to comply with guidanceUndergo cesarean birth during labor

Eligibility criteria for midwives.

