### Participants

All participants will be recruited from the Fourth Hospital of Shijiazhuang, Hebei Province, China. In total, 105 women will be recruited to receive the intervention. At the same time, 105 sets of medical notes will be identified, and relevant information will be extracted to compare health outcomes between the 2 cohorts. These medical notes will be from women who received standard care, that is, “directed pushing” during the second stage and met the same selection criteria as the women in the spontaneous pushing group. The women whose notes will be reviewed will not be recruited into this study, but permission has been obtained from the site-specific hospital to examine the deidentified medical notes. The demographic data, that is, age and the parity and labor care section of the medical notes will be reviewed and examined and parity in 2 cohorts will be matched for further comparison.

Six midwives will be recruited to support spontaneous pushing. They will be rostered to cover all 4 shifts of the roster to ensure that every recruited woman will be supported to push spontaneously by a recruited and trained midwife. All recruited midwives will be interviewed for the qualitative study part.

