### Recruitment

#### Recruitment of Women

The researcher (JY) will approach and recruit women into the study during their third trimester of pregnancy. This will allow the women to have enough time to read the information leaflet for the study, ask any questions, and make an informed decision about participating in the study without any undue pressure.

The study will be advertised using posters and information leaflets in the antenatal services of the hospital. The researcher (JY) will approach women while they are in the waiting room awaiting their appointment and will talk to them about the study assessing their willingness to receive further information about the study. Verbal information and a written information sheet outlining the study will be provided to the women to take home and review again before their next visit. At the women’s subsequent visit, the researcher (JY) will meet women who are willing to participate, provide them with an opportunity to ask any further questions about the research, and seek their consent to participate in the study by asking them to sign a consent form.

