#### Participants’ Safety and Withdrawal

A participant (including laboring women or midwives) may choose to withdraw from the study at any time. With consent, data before participant withdrawal will be retained and used in data analysis. Participant withdrawal may happen for several reasons, including but not limited to the following: (1) participant decision, (2) inability to comply with study procedures, and (3) the occurrence of what the participant perceives as an intolerable adverse effect.

In addition, the chief researcher (KB) will exclude a participant if it is considered necessary for any reason, including but not limited to (1) clinical decision, (2) ineligibility (either arising during the study or retrospectively having been overlooked at screening), (3) significant protocol deviation, and (4) significant noncompliance with intervention.

The nature and reason for the withdrawal or discontinuation will be recorded.

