#### Secondary Outcomes

Secondary outcomes will include the duration of the second stage of labor, maternal pushing position, mode of birth, rates of cesarean birth, perineal laceration, the rates of episiotomy, newborn Apgar scores, rates of newborn resuscitation, and rates of transfer to the neonatal intensive care unit. Table 5 illustrates the primary and secondary objectives, outcomes, criteria for success, methods for analysis, and measurement tools.

**Table 5 table5:** Primary and secondary outcome criteria, analysis, and measurement.

Objectives, outcomes, and criteria for success				Methods of analysis		Measurement or tool
**Primary objectives: To test the feasibility of a future RCT^a^ to compare the effects of spontaneous pushing and directed pushing for maternal and neonatal outcomes**						

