	**Mode of birth**					
		Normal vaginal birth, forceps extraction, vacuum extraction, breech delivery, and cesarean birth	n (%) for categorical variables		Case report forms	

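### Cesarean during labor is both an exclusion and a secondary outcome, so the cesarean comparison is fixed at 0% v 0%, or biased if only the control notes are filtered

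*Protocol article*

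**What the plan says.** All places are in the protocol article.

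- **Exclusion criteria for women:** the last listed item is cesarean birth during labor ("comply with guidanceUndergo cesarean birth during labor"; the first words belong to the item before it). Another item excludes any complication that affects how the second stage is managed.
- **Inclusion criteria for women:** an uncomplicated labor is required ("cephalic presentationNo complications during labor", again two items run together). Neither complication item says up to what moment it applies.
- **Control notes:** under Participants they must have "met the same selection criteria as the women in the spontaneous pushing group". Eligibility Criteria repeats this: "met the same eligibility criteria as the women in the spontaneous pushing group".
- **Outcomes:** Secondary Outcomes lists "mode of birth, rates of cesarean birth, perineal laceration, the rates of episiotomy, newborn Apgar scores, rates of newborn resuscitation", with duration of the second stage and neonatal intensive care transfer. Table 5 gives mode of birth the categories "Normal vaginal birth, forceps extraction, vacuum extraction, breech delivery, and cesarean birth". The case report form section lists cesarean again.
- **Timing and removal:** the researcher "will approach and recruit women into the study during their third trimester of pregnancy". A participant may later be excluded for "ineligibility (either arising during the study or retrospectively having been overlooked at screening").
- **Analysis:** Data Analysis names intention-to-treat for quantitative data and a Pearson chi-square test for categorical variables.

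**The concern.** A cesarean in labor can only be known once it happens. For women enrolled before labor, the criterion can act only by removing them after enrollment. For the control notes, it acts by selecting on an outcome that is already recorded. The Background section itself reports that women pushing spontaneously are less likely to have a cesarean in labor, so the plan makes eligibility depend on something its own rationale says the pushing strategy changes.

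The secondary objective, comparing maternal and neonatal outcomes between the two strategies, is at stake. The design is labelled noninferiority, and dropping adverse courses from both cohorts makes them look more alike. The study is also meant to supply estimates for a full trial, and the same criteria could be carried into it.

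**Working it through.** **Inputs.** The cohort size of 105 comes from Sample Size Determination. It rests on duration of the second stage, not on cesarean, and serves here only as a denominator. The article gives no cesarean rate, so the rates below are assumptions shown over a range. Let p_D and p_S be the true cesarean rates under directed and spontaneous pushing.

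**Reading 1: the exclusion is applied to both cohorts.** Every cesarean is removed from both numerators and denominators.

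- Observed rates: 0% and 0%. Observed difference: 0, whatever p_S − p_D is.
- Pearson chi-square: the expected count in each cesarean cell is 105 × 0/210 = 0, so the statistic divides by zero and is undefined.
- The result holds for any denominator. With the planned 20% dropout, 105 × 0.8 = 84, and 0/84 v 0/84 is equally empty.

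**Reading 2: intention-to-treat keeps enrolled women who have a cesarean, but control notes are still selected to contain none.**

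- Observed difference: p_S − 0. True difference: p_S − p_D. Bias: p_D, always against spontaneous pushing.

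| Assumed p_D v p_S | Expected cesareans in 105 v 105 | True difference (points) | Reading 1 shows | Reading 2 shows (points) |
|---|---|---|---|---|
| 2% v 2% | 2.1 v 2.1 | 0 | 0 | +2 |
| 5% v 5% | 5.25 v 5.25 | 0 | 0 | +5 |
| 5% v 2% | 5.25 v 2.1 | −3 | 0 | +2 |
| 2% v 10% | 2.1 v 10.5 | +8 | 0 | +10 |
| 5% v 15% | 5.25 v 15.75 | +10 | 0 | +15 |

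In the third row a true benefit of spontaneous pushing appears as harm. In the second row, rounding 5.25 to 5 gives 5/105 v 0/105:

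- Pearson chi-square = 210 × (5 × 105 − 100 × 0)² / (105 × 105 × 5 × 205) = 5.12, p = 0.024 without continuity correction.
- Fisher exact p = 0.060.

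Two equal strategies would therefore give a nominally significant result on the planned test.

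**The other outcomes.** Forceps and vacuum birth, low Apgar score, resuscitation and intensive care transfer are not named as exclusions, so they are not zero by construction. They can be lost in two ways: with the women removed for cesarean, and through the complication items if these are applied to events after pushing starts. The article does not say whether they are, and it allows removal for ineligibility that arises during the study. The size of this truncation cannot be computed from the document.

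**The case against.** **The effectiveness outcomes are secondary and exploratory.** The primary outcomes are feasibility and acceptability, and Table 5 shows only descriptive summaries for effectiveness. This stands as a limit on the consequence: the primary outcomes are untouched. It does not remove the contradiction, because a descriptive 0% v 0% is as uninformative as a test of it, and Data Analysis does add tests.

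**The complication items may be meant for conditions present before pushing, and excluding women whose cesarean precedes the second stage is reasonable.** This also stands as a possible reading. The fault is the missing time anchor; deletion of every later event is not demonstrated. The cesarean item is different: it covers labor as a whole, including the second stage.

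**A reader might infer that all harm is deleted, including instrumental births and sick newborns.** The document does not support that. Forceps and vacuum remain reportable categories, and no newborn event is an exclusion. Only cesarean is literally both an exclusion and an outcome.

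**A reader might infer that adverse events go unrecorded.** The document does not support that either. The reason for every withdrawal or discontinuation is recorded, and the retention criteria count recruited women who do not complete spontaneous pushing. The women leave the comparison, not the record.

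**Table 5 lists breech delivery although eligibility requires cephalic presentation.** This is a harmless empty category and adds nothing to the point.

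**Conclusion.** The point holds and is wrong as written. Under the stated criteria the cesarean comparison is 0% v 0% regardless of the truth, which needs no assumption beyond applying the text. If intention-to-treat overrides the exclusion for enrolled women, the contrast is biased against spontaneous pushing by the full directed-pushing rate: 2 to 5 points at assumed rates of 2% to 5%. Neither reading gives a valid cesarean comparison.

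For duration, instrumental birth, Apgar score, resuscitation and intensive care transfer, truncation is possible but its extent is unknown, and it depends on how the complication items are applied. It would be too strong to say that the whole effectiveness comparison is uninterpretable: perineal laceration and episiotomy, for example, are naturally assessed among vaginal births. The damage is confined to the secondary objective and to the estimates intended for the future trial.

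**What to change.** Reconcile the eligibility lists, the removal rule under Participants' Safety and Withdrawal, the outcome list, Table 5 and the intention-to-treat sentence, as follows:

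- Define the comparison set by status at full cervical dilation, which Table 5 already uses as the start of the second stage: no epidural, no disqualifying complication and no cesarean up to that point.
- Select the directed-pushing notes by the same rule, without regard to what happened afterwards.
- Count every later cesarean or complication as an outcome in the analysis set, and do not remove women from the comparison for it.
- Report enrolled women who leave before full dilation under retention, with reasons.

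This changes eligibility for analysis only, not care. Data collection ended in October 2023, so the cost is revised wording, re-screening of the control notes, and retrieval of outcome data from the notes of women already removed, where their consent allows. If some cannot be retrieved, their number and recorded reasons should be reported beside the comparison. The same definition should be carried into the future trial.

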**Inclusion criteria**
Qualified with a certificate in maternal and neonatal care by the Ministry of Health, People’s Republic of ChinaEmployed at the Birth Centre of the Fourth Hospital of Shijiazhuang, Hebei Province, ChinaProviding care at the birth siteWilling to participate (not allocated by a manager)Have at least 1 year of postregistration practice
**Exclusion criteria**
Unwilling to participateAllocated by a manager to participateDoula or other nonregistered lay birth support person

### Recruitment

#### Recruitment of Women

The researcher (JY) will approach and recruit women into the study during their third trimester of pregnancy. This will allow the women to have enough time to read the information leaflet for the study, ask any questions, and make an informed decision about participating in the study without any undue pressure.

The study will be advertised using posters and information leaflets in the antenatal services of the hospital. The researcher (JY) will approach women while they are in the waiting room awaiting their appointment and will talk to them about the study assessing their willingness to receive further information about the study. Verbal information and a written information sheet outlining the study will be provided to the women to take home and review again before their next visit. At the women’s subsequent visit, the researcher (JY) will meet women who are willing to participate, provide them with an opportunity to ask any further questions about the research, and seek their consent to participate in the study by asking them to sign a consent form.

#### Recruitment of Midwives

Study information will be shared at one of the midwives’ regular meetings or workshops and written information will be provided. Midwives will be encouraged to take the information sheet home to review, and those interested in participating in the study will be encouraged to contact the research team.

Upon permission, recruited midwives will be recruited to participate in a preparation program, which will be in a workshop format. The workshop will help to prepare them to provide care to women in the spontaneous pushing group. At the end of the study, the midwives will all be invited to attend a focus group interview to gain their views and thoughts about the implementation of the study, the intervention, and their experience of participating in the study. Midwives will not be rewarded for participating in the study. With permission from the birth center manager, the participation of midwives will occur during their normal working hours.

### Patient and Public Involvement

Patients and the public were not directly involved in the development of this protocol. However, the development of the research question and the preparation program content are in accordance with the previously published studies on laboring women’s and midwives’ experiences and priorities.

### Ethical Considerations

#### Ethics Approval

All the methods will be performed in accordance with the relevant guidelines and regulations. The protocol is approved by 2 ethical committees, the University of Technology Sydney Medical Research Ethics Committee (ETH22-7072) and the Health Research Committee from The Fourth Hospital of Shijiazhuang, Hebei Province, China (20230064). All participants will be provided with informed written consent prior to their enrollment in the study. Deidentified findings of this study will be shared locally via staff forums and education sessions in China; shared through peer-reviewed journal publications, international conferences, and seminar presentations; and included as part of the first author’s (JY) PhD thesis.

#### Informed Consent

Informed consent from both women and midwives will be obtained. A member of the research team (JY) will discuss the study with the women and midwives and provide them with details about the study and obtain written consent. All participants will not receive any type of compensation from the study.

All women participating in the study will be given a study code number, and this will be documented in their medical records and all study documents. A sticker with the logo of this study will be tagged in the top right corner of the participant’s medical notes. This will help midwives identify the recruited women when they arrive at the birth center in labor.

#### Participants’ Safety and Withdrawal

A participant (including laboring women or midwives) may choose to withdraw from the study at any time. With consent, data before participant withdrawal will be retained and used in data analysis. Participant withdrawal may happen for several reasons, including but not limited to the following: (1) participant decision, (2) inability to comply with study procedures, and (3) the occurrence of what the participant perceives as an intolerable adverse effect.

In addition, the chief researcher (KB) will exclude a participant if it is considered necessary for any reason, including but not limited to (1) clinical decision, (2) ineligibility (either arising during the study or retrospectively having been overlooked at screening), (3) significant protocol deviation, and (4) significant noncompliance with intervention.

The nature and reason for the withdrawal or discontinuation will be recorded.

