**Assessment**											
	Case report forms							✓			
	Survey for women									✓	

**Table 3 table3:** Chart of the study design, visits, and assessment for midwives.

Time point			Visit 1: before the preparation program		Visit 2: during the preparation program		Visit 3: during women’s labor		Visit 4: at the end of the study

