#### Survey for Women

A questionnaire with closed-ended and open-ended questions will be used to explore women’s satisfaction with pushing, their childbirth experience, and their experience in joining the study. The researcher (JY) will access women during their stay in the postnatal ward for the completion of the survey. In case women withdraw from the study, for personal or medical reasons, a withdrawal note will be recorded in their CRF.

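### The withdrawal rule provides only for data from before withdrawal, so birth outcomes of women who withdraw in labor are not secured, against the stated intention-to-treat analysis

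*Protocol article*

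**What the plan says.** All places are in the protocol article.

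- **Participants' Safety and Withdrawal.** A participant "may choose to withdraw from the study at any time". The listed reasons include inability to comply with procedures and "the occurrence of what the participant perceives as an intolerable adverse effect". The data provision reads: "With consent, data before participant withdrawal will be retained and used in data analysis". Nothing is said about data arising afterwards. The chief researcher may also exclude a woman, among other grounds for "significant noncompliance with intervention". The section closes: "The nature and reason for the withdrawal or discontinuation will be recorded".
- **Survey for Women.** "In case women withdraw from the study, for personal or medical reasons, a withdrawal note will be recorded in their CRF".
- **Table 2.** Spontaneous pushing is delivered at Visit 3, the second stage. The row "Case report forms" is ticked, as far as the extracted table shows, at Visit 4, within two hours after birth.
- **Case Report Form.** The researcher extracts the effectiveness outcomes from the medical notes. Pushing position is the exception: the midwife is asked for it.
- **Participants.** Controls are deidentified notes of women who are not recruited.
- **Data Analysis.** Quantitative data are to be analysed by intention to treat.

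**The concern.** The withdrawal section does not distinguish a woman who stops pushing spontaneously from one who no longer wants her records used. Both fall under a rule that speaks only of data collected so far. For an outcome measured repeatedly over months, such a rule would cost part of a series. Here the exposure is the second stage itself and the outcomes follow immediately, so a withdrawal during pushing comes before almost everything the study would compare.

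The loss can arise only in the intervention cohort, and one named route into it is an adverse effect. Secondary Outcomes lists no separate adverse-event outcome. Mode of birth, laceration, Apgar score, resuscitation and transfer to intensive care are therefore the main safety data for what the Aims section calls a change of practice. If the women who leave are those at higher risk, the safety description and the cohort comparison both shift in favor of spontaneous pushing.

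**Working it through.** **1. Which outcomes exist before birth (Table 5 and Case Report Form)**

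- Second-stage duration starts before birth but is complete only at delivery.
- Mode of birth, Apgar score, resuscitation and intensive-care transfer do not exist before birth.
- The final laceration grade is settled only with birth.
- Episiotomy precedes delivery, but only just.
- Pushing position is observed before birth.

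For a woman who withdraws during pushing, the data in hand are therefore pushing position and little else. A woman who withdraws after birth can keep her birth outcomes, with consent.

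**2. The provisions side by side**

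Intention to treat needs an outcome for every woman in the cohort, whether or not she kept to the intervention. The withdrawal rule provides for data up to withdrawal and for nothing later. If that is all that is used, a woman who withdrew in labor has missing outcomes and the comparison becomes one of those who stayed. The power to exclude for noncompliance is a separate provision, but it pulls the same way.

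**3. The plan's own figures**

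The planned size is 105 per group with 20% dropout: 105 × 0.20 = 21 women, leaving 84. Table 5 accepts loss to follow-up below 30%: 105 × 0.30 = 31.5. Sample Size Determination states no effect size, SD or margin, so 105 cannot be reproduced; the point does not depend on it. Both percentages cover loss from all causes. They serve below only as outer values, not as estimates of withdrawal in labor.

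**4. How much could be lost (assumed inputs)**

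Let N = 105, p = true event rate in all women, w = share withdrawing before birth, and RR = risk in withdrawers relative to the others. The observed rate is the rate r among those who stay:

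- r = p / (w·RR + 1 − w)
- events lost = N·w·RR·r

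With p assumed to be 10%, there are 10.5 true events:

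| w | RR = 1 | RR = 2 | RR = 3 |
|---|---|---|---|
| 5% | 10.0% | 9.5% | 9.1% |
| 20% | 10.0% | 8.3% | 7.1% |
| 30% | 10.0% | 7.7% | 6.3% |

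Worked cell, w = 20%, RR = 3: r = 0.10 / (0.60 + 0.80) = 0.0714. Events lost = 105 × 0.20 × 3 × 0.0714 = 4.5. Check: (10.5 − 4.5) / 84 = 7.1%.

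At w = 20% the events lost are 2.1, 3.5 and 4.5 for RR = 1, 2 and 3. The count falls in every case, but the rate falls only when RR exceeds 1. If outcomes are still read from the notes after withdrawal, the observed rate is 10% in every cell.

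**The case against.** The strongest reply is that the text does not forbid later extraction. It says that earlier data will be kept and is silent on the rest. The intention-to-treat statement, with outcomes drawn from routine notes, can be read as covering women who stop. Session 5 of the midwives' program teaches withdrawal options and a safety protocol, so fuller procedures exist, and an article may leave them to the full protocol. The outcomes concerned are secondary; the primary ones are feasibility and acceptability.

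Much of this stands. That only earlier data will be used is the natural reading, not an express prohibition. But the article itself states a data rule and an analysis principle that pull apart, so this is more than omitted detail.

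A reader might also infer four stronger things that the documents do not support:

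- **That a withdrawal note takes the place of the outcomes.** Survey for Women says that "a withdrawal note will be recorded in their CRF"; this adds an entry and does not say that other fields stay blank.
- **That such withdrawals are invisible.** Their nature and reason are recorded, so they can at least be counted.
- **That the control cohort keeps all its bad outcomes.** The audited notes must meet the same eligibility criteria, which screen out complications in labor and cesarean birth during labor. What holds is narrower: controls have no withdrawal process.
- **That a withdrawn woman contributes no outcome at all.** This fails for pushing position and for withdrawal after birth.

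**Conclusion.** The point holds as an unresolved conflict between the withdrawal rule and the intention-to-treat statement. Applied as written, the rule does not secure birth outcomes for women who withdraw in labor, and this gap exists in the intervention cohort only.

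It would go too far to conclude that harm is under-counted. That requires withdrawal before birth to be related to harm. Listing an adverse effect as a withdrawal reason makes this plausible, but the documents give neither a withdrawal rate nor an event rate. On the assumed 10% event rate, the effect runs from none (unrelated withdrawal) through 9.1–9.5% (5% withdrawing, risk two to three times higher) to 6.3% (30% withdrawing, risk three times higher).

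The consequence is moderate. Secondary outcomes are affected, but the study is meant to inform a larger trial, and the correction is cheap.

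**What to change.** Reconcile Participants' Safety and Withdrawal, Survey for Women and Data Analysis by separating two events:

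- **(a) Stopping spontaneous pushing.** The woman stays in the intention-to-treat cohort and her full case report form is extracted from the medical notes as for any other woman.
- **(b) Refusing use of her records.** The refusal is honored, and the number of such women and their reasons are reported.

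State that the withdrawal note is entered in addition to the outcome fields. Tabulate the outcomes of women who stopped.

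The Results section puts data collection between May and October 2023, so consent wording cannot be changed for these women. For the present data, apply (a) where existing consent allows, and say for how many women it does not. For the future randomized trial, put permission for continued record extraction into the consent form.

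The cost is revised wording, a few more extractions from notes the hospital already holds, and possibly less favorable event rates for spontaneous pushing.
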